**Conclusions:**

This study will define the genetic risk related to 3 marker genes proposed in a pharmacogenetic guideline for risk assessment. Moreover, the results of this study will show the prevalence of cardiovascular dysfunction in survivors of pediatric neuroblastoma or nephroblastoma who were treated with doxorubicin. The results will help to improve primary treatment and follow-up care, thus reducing cardiovascular late effects in the growing population of childhood cancer survivors.

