### Estimation of Case Numbers for the Pharmacogenetic Studies

The appropriate case number was estimated based on a published study of the association of the nonsynonymous *RARG* gene variant p.Ser427Leu (rs2229774) with anthracycline-induced cardiomyopathy (combined analysis of the discovery and replication cohorts: odds ratio 4.7, 95% CI 2.7-8.3; *P*<.001) [12]. Assuming an odds ratio of 4.7, an allele frequency (controls) of 6.4%, an alpha error of 5%, power of 80%, a control: case ratio of 3:1, and a dropout rate of approximately 10%, at least 33 cases and 99 controls, will be required to replicate with sufficient statistical power the association of *RARG* rs2229774 with anthracycline-induced cardiomyopathy.

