^c^UGT1A6: UDP glucuronosyltransferase family 1 member A6.

^d^SLC28A3: solute carrier family 28 member 3.

Our secondary aim is to replicate the previously described associations of candidate genetic markers with anthracycline-induced cardiotoxicity if our sample size has sufficient statistical power. Association of the candidate SNPs with the outcome will be performed using logistic regression, adjusting for sex; age; mediastinal, left abdominal, and lung irradiation; the use of other cardiotoxic drugs; length of follow-up; and cumulative dose of doxorubicin. The Benjamini-Hochberg False Discovery Rate will be used to account for multiple testing.

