### Genotyping

We received biomaterial from 480 patients: 456 EDTA blood samples and 24 saliva samples. DNA was extracted and genotyped for *RARG* rs2229774, *SLC28A3* rs7853758, and *UGT1A6* rs17863783. Genotype frequencies for the candidate SNPs are summarized in Table 6. The call rate was 100% for all SNPs. All SNPs passed the HWE test at *P*>.01. Table 7 summarizes the numbers of patients in each genetic risk group, scored according to the CPNDS Clinical Practice Recommendations Group [14] and based on multimarker genetic testing for *RARG* rs2229774, *UGT1A6* rs17863783, and *SLC28A3* rs7853758.

**Table 6 table6:** Genotype frequencies in the study cohort of neuroblastoma and nephroblastoma patients.

SNP^a^ and genotype		N	*P-*HWE^b^
*RARG*^c^ rs2229774			
	G/G	419	0.9604
	A/G	59	
	A/A	2	
*SLC28A3*^d^ rs7853758			
	G/G	355	0.848
	A/G	115	
	A/A	10	
*UGT1A6*^e^ rs17863783			
	G/G	467	0.764
	T/G	13	
	T/T	0	

^a^SNP: single nucleotide polymorphism.

^b^*P*-HWE: Hardy-Weinberg equilibrium χ^2^ test *P*-value

^c^RARG: retinoic acid receptor gamma.

^d^SLC28A3: solute carrier family 28 member 3.

^e^UGT1A6: UDP glucuronosyltransferase family 1 member A6.

**Table 7 table7:** Genetic risk categories observed in our study population. Genetic risk scoring was performed according to the recommendations of the Canadian Pharmacogenomics Network for Drug Safety Clinical Practice Recommendations Group [14].

Genetic risk	Observed, n (%)
High	72 (15.0)
Moderate	301 (62.7)
Low	107 (22.3)
Total	480 (100)

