Although study limitations, such as the variable follow-up time and the low participation rate, will have to be considered, our study will define for the first time the combined genetic risk related to three marker genes proposed for risk assessment in the CPNDS pharmacogenetic guidelines. Moreover, the results of this study will identify the prevalence of cardiovascular dysfunction among survivors of pediatric neuroblastoma or nephroblastoma treated with doxorubicin. The results will help to improve primary treatment and follow-up care to reduce cardiovascular late effects in the growing population of childhood cancer survivors.

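### With 13 carriers among 480 patients, a separate UGT1A6 odds ratio would be very imprecise; name a sparse-data method and limit the abstract's claim to combined risk

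*Protocol article*

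**What the plan says.** - **Single-marker analysis** (Methods, Statistical Analysis): "Association of the candidate SNPs with the outcome will be performed using logistic regression", adjusted for sex, age, irradiation, other cardiotoxic drugs, length of follow-up and cumulative doxorubicin dose. Benjamini-Hochberg control follows. The preceding sentence makes this aim conditional on sufficient power and gives no threshold.
- **Which markers it covers.** The last paragraph of the Introduction describes the secondary aim as concerning other candidate genes. Results, Genotyping says "Genotype frequencies for the candidate SNPs are summarized in Table 6", and Table 6 contains exactly the three guideline markers.
- **Data.** "We received biomaterial from 480 patients: 456 EDTA blood samples and 24 saliva samples". Table 6 gives UGT1A6 as 467 G/G, 13 T/G and 0 T/T.
- **Primary aim.** UGT1A6 enters only through a three-level score that pools T carriers with RARG A carriers as high risk (72 patients, Table 7).
- **Sample size.** Only RARG is covered: "Assuming an odds ratio of 4.7", with a requirement of at least 33 cases and 99 controls.
- **Claims.** Abstract, Conclusions: "This study will define the genetic risk related to 3 marker genes proposed in a pharmacogenetic guideline for risk assessment". Discussion, last paragraph: "our study will define for the first time the combined genetic risk related to three marker genes".

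**The concern.** Thirteen carriers is very little information for one coefficient in a multivariable model. If none of the cases is a carrier, the maximum-likelihood odds ratio goes to zero and a Wald interval cannot be formed. If a few cases are carriers, the estimate exists but its interval spans roughly an order of magnitude or more. The article reports the sparse count and names ordinary logistic regression without addressing it.

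The abstract, read alone, suggests that the risk belonging to each of three genes will be established. A reader could then take a result for the high-risk class, which consists mainly of RARG carriers, as evidence about UGT1A6.

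**Working it through.** **1. The plan's own figure (RARG).** Control carrier frequency is 1 - (1 - 0.064)² = 0.124. At an odds ratio of 4.7 the case frequency is 4.7 × 0.124 / (1 - 0.124 + 4.7 × 0.124) = 0.399. A two-sided 5% test (sidedness is not stated) with 80% power, a 3:1 ratio and continuity correction needs 28.1, so 29 cases. Then 29 / 0.9 = 32.2, so 33 cases and 99 controls. The figure reproduces. There is no counterpart for UGT1A6.

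**2. Carriers.** The reference frequency of 0.023 in Table 2 implies 480 × [1 - (1 - 0.023)²] ≈ 22 carriers; 13 were found (2.7%). In the high-risk class, 61 RARG carriers + 13 UGT1A6 carriers - 72 patients = 2 carry both. So 13 - 2 = 11 of 72 (15%) are there through UGT1A6 alone.

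**3. Outcome prevalence.** This is not reported. The range 4.4%-42%, which the Introduction cites from earlier studies, is used as an assumption. It corresponds to about 21 to 202 cases in 480.

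**4. Precision near the null.** For *a* carriers among *k* cases, take *b* = *k* - *a*, *c* = 13 - *a* and *d* = 480 - *k* - *c*. The interval is (*ad*/*bc*) × exp(±1.96 √(1/*a* + 1/*b* + 1/*c* + 1/*d*)).

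| Cases | Carriers among cases | OR | SE(log OR) | 95% CI |
|---|---|---|---|---|
| 33 | 1 | 1.13 | 1.057 | 0.14-9.0 |
| 120 | 3 | 0.90 | 0.667 | 0.24-3.3 |
| 202 | 5 | 0.86 | 0.578 | 0.28-2.7 |

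Even at 202 cases the limits differ by a factor of 9.6. In a simulation with six covariates (distributions and effects assumed, 1,500 runs per scenario), the median ratio of upper to lower limit was about 11 to 71.

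**5. Power.** With 13 carriers against 467 non-carriers, Fisher's exact test has 9%-22% power at OR 2, 20%-48% at OR 3 and 41%-77% at OR 4.7 over the prevalence range. By normal approximation 80% is only just reached at OR 4.7, at 30% prevalence.

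**6. Chance of no finite estimate.** With prevalence *p* in non-carriers and no effect, P(no case among 13 carriers) = (1 - *p*)¹³. The last column fixes the number of cases (hypergeometric).

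| Prevalence | Cases | (1 - *p*)¹³ | Fixed case count |
|---|---|---|---|
| 4.4% | 21 | 0.557 | 0.555 |
| 6.9% | 33 | 0.395 | 0.391 |
| 10% | 48 | 0.254 | 0.250 |
| 20% | 96 | 0.055 | 0.053 |
| 25% | 120 | 0.024 | 0.022 |
| 42% | 202 | 0.001 | 0.001 |

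At OR 2 the chance is 32% at 4.4% prevalence and 7% at 10%. At OR 4.7 it is 8% and 0.4%. The adjusted simulation under no effect gave 49%, 19%, 3% and 0.1% at prevalences of 4.4%, 10%, 20% and 42%.

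**7. What other methods give with no carrier among cases.** The exact conditional upper 97.5% limit for the odds ratio is 4.5 with 33 cases and 3.0 with 48. For 0 carriers among 33 cases, the unadjusted likelihood-ratio P value is 0.17 and the profile upper limit is about 2.2 (approximate with data this sparse).

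**The case against.** - **Frequency of failure.** A reader might infer that ordinary logistic regression will often be unable to estimate the odds ratio. That needs an outcome prevalence of about 10% or less and a null or small effect. The primary endpoint is met by any one of seven criteria, so prevalence may be well above that. The 33 cases are a minimum at a 3:1 ratio, not a forecast for 480 patients; the same ratio in 480 gives 120 cases and a 2% chance of failure. This objection stands.
- **P value.** A reader might infer that the P value passed to Benjamini-Hochberg would be meaningless. That follows only for Wald tests. The article names no test, and the likelihood-ratio test still works (step 7). This stands.
- **Scope.** The secondary aim depends on sufficient power and may not include UGT1A6. This stands in part. The condition has no threshold, and the article's use of the term candidate SNPs points the other way from the Introduction. If the condition excludes UGT1A6, no marker-specific result will exist, and the abstract's wording is still too broad.
- **Promise.** A reader might infer that the study promises something it cannot deliver for UGT1A6. The Discussion claims only combined risk, which the pooled score can address. Only the abstract is looser.
- **Level of detail.** Choosing a sparse-data method can be left to an analysis plan, and this is a condensed article. That limits the point to an improvement on the stated method and a wording correction. The sparse count is already known, however, so there is reason to settle the method now.

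**Conclusion.** The point holds in a limited form. The firm part is imprecision: 13 carriers cannot give a usefully narrow separate odds ratio for UGT1A6 anywhere in the assumed 4.4%-42% prevalence range, and power is low for moderate effects. Outright failure of the maximum-likelihood estimate is a conditional risk: under no effect, 25% at 10% prevalence rising to 56% at 4.4%, and about 5% or less at 20% and above. All of this applies only if UGT1A6 is analysed singly, which the article leaves open.

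The documents do not support extending the point to the primary analysis. Its models use the three-level score and fit no UGT1A6 coefficient. The abstract's claim is broader than the data allow for this marker; the Discussion's claim is not.

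**What to change.** 1. Fit the candidate-SNP models by Firth penalised likelihood, with profile-likelihood intervals and penalised likelihood-ratio P values for the Benjamini-Hochberg step. Add an exact conditional analysis for UGT1A6 as a check.
2. State whether the three guideline markers are part of the single-marker analysis, so that the Introduction and the Results agree.
3. In the abstract's conclusions, refer to combined genetic risk, in line with the Discussion, which needs no change. Add that with 13 carriers the study can only bound UGT1A6's separate effect.

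The article says the database is not yet closed, so this can be settled before analysis. The cost is standard software, a few sentences and a slightly less favourable claim for one marker. There is no gain in power: in a simulation with eight assumed covariates, 33 cases and OR 4.7, Firth and ordinary maximum likelihood each had about 55%. The gain is a finite estimate with a usable interval in every data configuration.

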## Results

### Recruitment

This cohort study evaluates the risk of developing anthracycline-induced cardiotoxicity in survivors (ie, survival for 5 years or more after diagnosis) of pediatric nephroblastoma or neuroblastoma. A review of the German Childhood Cancer Registry database revealed 2158 eligible patients (943 nephroblastoma and 1215 neuroblastoma patients) who were invited by mail to participate in the study (Figure 1).

Patient recruitment started in June 2017 and was completed in September 2018. There were 657 patients (284 neuroblastoma and 373 nephroblastoma patients) who consented to participate in the LESS-Anthra study, and 480 (73%) of these patients provided a biospecimen for pharmacogenetic studies. Table 4 summarizes the baseline characteristics of participants and nonparticipants of LESS-Anthra.

**Figure 1 figure1:**
[figure not shown]
Flowchart of patients’ inclusion or exclusion.

**Table 4 table4:** Comparison of baseline characteristics of participants and nonparticipants of the LESS-Anthra study.

	Patients invited for participation (n=2158)	Nonresponders, no consent, or refusal (n=1499)	Participants (n=657)
Age at diagnosis (years), median (range)	2.0 (0-17)	2.0 (0-17)	2.0 (0-17)
Follow-up time (years), median (range)	14.0 (5-27)	15.0 (5-27)	13.0 (5-27)
Proportion of male to female patients	1.0	0.9	1.2
Proportion of nephroblastoma to neuroblastoma patients	1.3	1.3	1.3

### Anthracycline Treatment

According to the respective protocol, and dependent on the stage and risk group, the cumulative dose of doxorubicin was 45-240 mg/m^2^ for neuroblastoma patients and 100-400 mg/m^2^ for nephroblastoma patients (Table 5).

**Table 5 table5:** Per protocol cumulative dose of doxorubicin used in the neuroblastoma (NB90, NB97, and NB 2004) and nephroblastoma (SIOP 9/GPOH, SIOP 93-01/GPOH, and SIOP 2001/GPOH) trials.

Study and study arm		Doxorubicin cumulative dose (mg/m^2^)	Single-dose, duration of IV^a^ application
**NB90**			
	Stage 2 or stage 3A-B	120	Course N2: 60 mg/m^2^, 48h Course N3: 15 mg/m^2^, slow IV injection
	Stage 3C-D or stage 4	240	
	Stage 4S	60	
**NB97**			
	Standard risk group	120	Course N6: 30 mg/m^2^, 4h Course N4: 0.5 mg/kg, 30min
	High-risk group	180	
**NB 2004**			
	Observation group with tumor progression	45 or 180 (depending on further progression after first cycle)	Course N6: 30 mg/m^2^, 4h Course N4: 15 mg/m^2^, 30min
	Medium risk group	180	
	High-risk group	180	
**SIOP 9/GPOH**			
	Stage II, Stage III	250	50 mg/m^2^, 4h
	Stage IV, no metastasis after preoperative chemotherapy	400	
	Stage IV, no CR after preoperative chemotherapy	100	
**SIOP 93-01/GPOH**			
	Stage II or III and low or intermediate risk by histology	250	50 mg/m^2^, 4h
	Stage II or III and high risk by histology	300	
	Stage IV	400	
**SIOP 2001/GPOH**			
	Stage I, high risk	250	50 mg/m^2^, 4-6h
	Stage II or stage III, intermediate-risk, randomized regimen AVD	250	
	Stage II or stage III, high risk	300	
	Stage IV	300	

^a^IV: intravenous.

### Genotyping

We received biomaterial from 480 patients: 456 EDTA blood samples and 24 saliva samples. DNA was extracted and genotyped for *RARG* rs2229774, *SLC28A3* rs7853758, and *UGT1A6* rs17863783. Genotype frequencies for the candidate SNPs are summarized in Table 6. The call rate was 100% for all SNPs. All SNPs passed the HWE test at *P*>.01. Table 7 summarizes the numbers of patients in each genetic risk group, scored according to the CPNDS Clinical Practice Recommendations Group [14] and based on multimarker genetic testing for *RARG* rs2229774, *UGT1A6* rs17863783, and *SLC28A3* rs7853758.

**Table 6 table6:** Genotype frequencies in the study cohort of neuroblastoma and nephroblastoma patients.

SNP^a^ and genotype		N	*P-*HWE^b^
*RARG*^c^ rs2229774			
	G/G	419	0.9604
	A/G	59	
	A/A	2	
*SLC28A3*^d^ rs7853758			
	G/G	355	0.848
	A/G	115	
	A/A	10	
*UGT1A6*^e^ rs17863783			
	G/G	467	0.764
	T/G	13	
	T/T	0	

^a^SNP: single nucleotide polymorphism.

^b^*P*-HWE: Hardy-Weinberg equilibrium χ^2^ test *P*-value

^c^RARG: retinoic acid receptor gamma.

^d^SLC28A3: solute carrier family 28 member 3.

^e^UGT1A6: UDP glucuronosyltransferase family 1 member A6.

**Table 7 table7:** Genetic risk categories observed in our study population. Genetic risk scoring was performed according to the recommendations of the Canadian Pharmacogenomics Network for Drug Safety Clinical Practice Recommendations Group [14].

Genetic risk	Observed, n (%)
High	72 (15.0)
Moderate	301 (62.7)
Low	107 (22.3)
Total	480 (100)

### Data Collection

We are in the final phase of data collection. Currently, final plausibility and quality checks are being performed before the closure of the database.

## Discussion

The CPNDS Clinical Practice Recommendations Group has issued a level B recommendation (moderate evidence base: at least one high-quality study or multiple moderate-quality studies) that pharmacogenomic testing for the variants *RARG* rs2229774, *SLC28A3* rs7853758, and *UGT1A6**4 rs17863783 should be performed in all pediatric cancer patients with an indication for doxorubicin or daunorubicin therapy to stratify their cardiovascular risk. The recommendation was based on a few studies investigating the separate effects of each of the genetic markers on anthracycline-induced cardiotoxicity. Additional studies are required to increase confidence in the genetic associations further.

This prospective cohort study is the first to evaluate the ability of combined testing for *RARG* rs2229774, *SLC28A3* rs7853758, and *UGT1A6**4 rs17863783, as recommended in the pharmacogenetic guidelines, to correctly predict doxorubicin-related cardiotoxicity in a large cohort of patients with consistent diagnoses. Strengths of this study include the homogeneity of the cohort in terms of diagnoses and treatment protocols, the fact that no anthracyclines other than doxorubicin were used, and the large sample size. Because echocardiographic findings are subject to inter‐reader variability, the original echocardiographic recordings will be evaluated in a standardized manner by a single pediatric cardiologist, thereby reducing potential bias. The image acquisition protocol guided the site sonographers in performing the echocardiographic examinations according to the specific needs of our trial. All these methods were designed to improve the accuracy of echocardiographic findings. Nevertheless, different producers of echocardiography equipment and software and site-specific machine settings can still contribute to the variability of findings.

Unfortunately, there is no generally accepted definition of anthracycline-induced cardiotoxicity based on echocardiography [20,24-26]. Currently, the Cardio-Oncology and Imaging Working Group of the German Society for Pediatric Cardiology and Congenital Heart Defects is preparing a position paper in collaboration with the GPOH and the German Society for Cardiology-Cardiovascular Research. This paper will standardize the specific echocardiographic parameters and thresholds that should be used to define normal or abnormal parameters in childhood cancer survivors treated with anthracyclines. Therefore, because this issue is not yet conclusively resolved, we may need to adjust the outcome definitions in our study, depending on the results of the upcoming guidelines.

The overall participation rate in the LESS-Anthra study was only 30%, and not all LESS-Anthra participants were also willing to participate in the pharmacogenetic substudy. The participation rate is at the lower end of the range of figures reported in the literature [27]. We attempted to give as many eligible patients as possible the opportunity to participate, regardless of whether or not they were followed up closely. This strategy required the rather impersonal approach of study invitation and study consent by mail. Recruitment would likely be more successful if limited to patients in regular follow-up care who were invited and personally approached by the follow-up physician. Helligsoe et al [27] addressed study participation in childhood cancer survivors in clinical late-effect studies [27]. The authors analyzed 80 published studies originating from 16 cohorts, with a median follow-up of 6.0 years. They found that overall participation rates ranged from 27% to 100% and speculated that more personalized recruitment strategies could increase participation rates. Our preliminary results confirm the finding that time since diagnosis does not influence participation [27]. Age at diagnosis also does not have a measurable impact. Interestingly, in LESS-Anthra, slightly more male patients were in the responder group than nonresponders (Table 5).

Although study limitations, such as the variable follow-up time and the low participation rate, will have to be considered, our study will define for the first time the combined genetic risk related to three marker genes proposed for risk assessment in the CPNDS pharmacogenetic guidelines. Moreover, the results of this study will identify the prevalence of cardiovascular dysfunction among survivors of pediatric neuroblastoma or nephroblastoma treated with doxorubicin. The results will help to improve primary treatment and follow-up care to reduce cardiovascular late effects in the growing population of childhood cancer survivors.

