The primary aim of this study is to evaluate the importance of multimarker genetic testing for *RARG* rs2229774, *UGT1A6* rs17863783, and *SLC28A3* rs7853758 for predicting doxorubicin-induced cardiovascular dysfunction. We focus on these 3 markers because the only pharmacogenetic guideline published to date recommends their testing to stratify the individual cardiotoxic risk of anthracycline therapy. The secondary aim of this study is to determine the association of doxorubicin-induced cardiovascular toxicity with other candidate genes that have been previously described [13,16-19] or will soon be discovered, provided that our sample size has sufficient statistical power. To ensure that the population studied is as homogeneous as possible in terms of diagnoses and the type of anthracycline used, we focus on patients with childhood nephroblastoma or neuroblastoma. Another secondary objective is to investigate the prevalence of cardiovascular dysfunction in a population of children treated with doxorubicin.

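### The Discussion says time since diagnosis did not affect participation, but Table 4 shows a 2-year gap in median follow-up, so selection on follow-up cannot be dismissed for the prevalence objective

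*Protocol article*

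**What the plan says.** The Discussion comments on who took part: "Our preliminary results confirm the finding that time since diagnosis does not influence participation". It makes a similar statement for age at diagnosis and then reports that "slightly more male patients were in the responder group than nonresponders". It gives no test or interval for any of these.

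The comparison is in Table 4 (Results, Recruitment). Median follow-up is 14.0 years in the invited cohort (n=2158), 15.0 in nonparticipants (n=1499) and 13.0 in participants (n=657). The range is 5-27 years in each column. The male-to-female ratio is 1.0, 0.9 and 1.2 respectively. Median age at diagnosis is 2.0 years throughout.

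Prevalence is a stated aim. The Introduction says: "Another secondary objective is to investigate the prevalence of cardiovascular dysfunction in a population of children treated with doxorubicin". Under Statistical Analysis, length of follow-up is one of the clinical risk factors in Model 1 and an adjustment variable in the candidate-gene analyses. The article does not say how prevalence will be estimated. The closing paragraph of the Discussion names variable follow-up and low participation as limitations.

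**The concern.** The sentence on time since diagnosis and the follow-up row of Table 4 cannot both stand as written. The sentence presents the study's own data as confirming no effect, yet the only data shown point to longer-surviving patients taking part less often.

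This matters most for prevalence. The Introduction describes cardiomyopathy that can appear years after treatment ends, and the models treat follow-up as a risk factor. If participation depends on follow-up and the outcome does too, prevalence among participants differs from prevalence among eligible survivors. Naming low participation and variable follow-up as separate limitations does not say that they are linked, and the Discussion sentence denies the link. A reader would conclude that no standardisation on follow-up is needed.

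**Working it through.** **The stated participation rate.** 657/2158 = 30.4%, which reproduces the 30% in the Discussion. With the 2173 given under Patients it is 30.2%.

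**Is follow-up in Table 4 time since diagnosis?** Eligible diagnoses run from 1990 to 2012 and recruitment began in 2017. 2017 - 2012 = 5 and 2017 - 1990 = 27, exactly the printed range. So yes.

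**Could the gap be chance?** The large-sample standard error of a difference of two medians is [1/(2f)] × √(1/657 + 1/1499), where f is the density at the median. The square root is 0.0468. No SD is given, so the spread is assumed:

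- Uniform over 5-27 years: f = 1/22, SE = 11 × 0.0468 = 0.515.
- Normal: SE = 1.2533 × SD × 0.0468, which is 0.293 for SD 5 and 0.411 for SD 7.

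All printed medians are whole numbers, so each may be off by half a year and the true gap may be as small as 1 year.

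| Assumed spread | z, 2-year gap | z, 1-year gap |
|---|---|---|
| Uniform 5-27 | 3.9 | 1.9 (p = 0.052) |
| Normal, SD 7 | 4.9 | 2.4 |
| Normal, SD 5 | 6.8 | 3.4 |

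The normal factor 1.2533 should not be paired with the SD of the uniform (22/√12 = 6.35). That mixture gives 5.4 for 2 years and hides that the least favourable case is borderline.

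**What this implies for participation.** Under the normal assumption, the share below 14 years is Φ(1/SD) in participants and Φ(-1/SD) in nonparticipants. For SD 5: 657 × 0.579 = 381 and 1499 × 0.421 = 631, so participation is 381/1012 = 38% below 14 years and 276/(276 + 868) = 24% above. For SD 7 the figures are 36% and 26%.

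**What it could do to prevalence.** Treating the medians as means, the average over the cohort is (657 × 13 + 1499 × 15)/2156 = 14.39 years, so participants lie 1.39 years below it. Shift the logit of the observed prevalence by 1.39 × ln(OR per year). The odds ratios are assumptions:

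| OR per year | If 10% observed | If 25% observed |
|---|---|---|
| 1.00 | 10.0% | 25.0% |
| 1.02 | 10.3% | 25.5% |
| 1.05 | 10.6% | 26.3% |
| 1.10 | 11.3% | 27.6% |

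The sampling half-width, 1.96 × √(p(1-p)/657), is 2.3 points at 10% and 3.3 points at 25%.

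**Sex.** The ratios give 1.2/2.2 = 54.5% male among participants and 0.9/1.9 = 47.4% among nonparticipants: z = 3.1, or 2.0 to 4.1 over the rounding of the ratios.

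**Tumour type.** Recruitment gives 943 nephroblastoma and 1215 neuroblastoma patients invited, a ratio of 0.78. Participants are 373 and 284, a ratio of 1.31. Subtraction leaves 570 and 931 nonparticipants, a ratio of 0.61. Table 4 prints 1.3 in all three columns. Taken as written, the counts give participation of 373/943 = 39.6% against 284/1215 = 23.4%. With the two invited counts exchanged, the ratios become 1.29, 1.31 and 842/659 = 1.28, and participation is 30.7% against 30.1%. The article does not show which is right.

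**The case against.** A reader might infer that the study will report an unweighted prevalence and that this figure is biased. The article supports neither claim. It gives no estimator, and a condensed article may leave that to the full protocol or analysis plan. A follow-up gap biases prevalence only if prevalence varies with follow-up in this cohort, and no such gradient is reported. Listing follow-up as a covariate makes bias plausible, not established.

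The direction is not certain either. Longer follow-up means an earlier trial, and Table 5 shows that planned doses differ between trials. Participation may also depend on current health, which is unknown in nonparticipants. Under the assumed gradients the shift is smaller than the sampling error.

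A reader might also count the sex ratio as a second contradiction. It is not one: the Discussion claims no influence only for time since diagnosis and age at diagnosis, reports the sex difference openly, and Table 4 agrees with it on age. Sex is evidence of selection, but disclosed.

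Finally, low participation is acknowledged, and Table 4 shows only summaries, so access to individual records of people who did not consent is not demonstrated.

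All of this limits the point. None of it reconciles the sentence with the follow-up row.

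**Conclusion.** The Discussion sentence is contradicted by Table 4. A 2-year gap is hard to put down to chance (z about 3.9 to 6.8). If rounding hides a 1-year gap the evidence runs from borderline to clear (1.9 to 3.4), and even then it does not confirm no influence. These values rest on assumed spreads.

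The prevalence objective is therefore at risk of bias, probably towards underestimation. The effect is zero if prevalence does not vary with follow-up, and about 0.3 to 1.3 points at 10% prevalence for odds ratios of 1.02 to 1.10 per year. Neither the presence nor the size of bias can be established from the article. The point is still worth acting on: prevalence is a stated aim, analyses were not complete at publication, and the remedy is cheap.

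**What to change.** 1. Correct the Discussion sentence, or replace it with the difference in follow-up between participants and nonparticipants and its confidence interval.
2. Beside the crude prevalence, report one standardised or inverse-probability weighted to the invited cohort on follow-up time, sex and age at diagnosis. If individual records of nonparticipants cannot be used, a cross-tabulation of the invited cohort by bands of these variables is enough for standardisation. State that this handles measured differences only.
3. Add tumour type only after the counts under Recruitment and the ratios in Table 4 are reconciled. At the same time, settle the cohort totals (1499 + 657 = 2156, against 2158 in Table 4 and 2173 under Patients) and the Discussion's reference to Table 5 for the sex comparison, which is in Table 4.
4. Weighting the step from 657 participants to 480 genotyped is optional, because the clinical and combined models and the candidate-gene analyses already adjust for follow-up and sex.

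The cost is one extra analysis and a slightly wider interval. As an illustration, take two follow-up bands and the SD 5 case: 381 participants with weight 1012/381 = 2.66 and 276 with weight 1144/276 = 4.14. The effective sample size is (Σw)²/Σw² ≈ 626, so the interval widens by √(657/626), about 2.5%. Adding sex and age would add somewhat to this.
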